### Randomization, allocation concealment, and blinding

The participants who fulfil the inclusion criteria will be randomly assigned to one of three groups (A, B, and C). Blank folders will be numbered from 1 to 69 and will be given concealed codes for the group assignment by an independent researcher and kept in a safe locker. When a participant is eligible and give their consent to participate, an independent therapist will draw the next folder from the file, which will determine the group assignment. A trained research assistant blinded to group assignment will record all measurements.

### Statistical analysis

Demographic data and baseline scores of all outcome measures will be presented to evaluate baseline comparability of treatment groups. Descriptive data will be reported for each group as the mean change in the outcome measures at baseline and at the end of the trial. Data normality will be tested. Paired t-tests and one-way ANOVA with Bonferroni adjustment for multiple comparisons will be applied to compare within and between group differences of all outcomes (interval/ratio data). The Wilcoxon signed-rank test and Friedman test will be used to compare within and between group differences of all outcome measures (nominal/ordinal data). The probability level for all tests will be set at 0.05 to indicate significance. The intention-to-treat principles will be used for analysis. For missing data, the last observation carried forward method will be used. All data will be analyzed using SPSS software version 22 (SPSS, Chicago, Illinois).

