### Outcome measures

Table 1 details the outcome measures that will be assessed to determine treatment effects. The primary outcome includes knee pain intensity and functional disability. The secondary outcome includes quadriceps muscle strength and functional mobility. All measurements will be taken at baseline (week 0), and at the end of the intervention (week 6).

**Table 1 Tab1:** Summary of outcome measures will be used to determine effectiveness of the treatment

Outcome	Measurement tool
Primary outcomes	
Knee pain	NRS, Reduced WOMAC pain subscale
Knee function	Reduced WOMAC physical function subscale
Secondary outcomes	
Isometric quadriceps muscle strength	Hand held dynamometer
Functional mobility	Timed up and go test

*NRS* numeral rating scale, *WOMAC* Western Ontario and McMaster Universities osteoarthritis index

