### Sample size

The statistical software Statmate version 2 (GraphPad Software, Inc., CA, USA) was used to calculate the sample size using the primary outcome variables, the NRS scores for pain and the reduced WOMAC index for function, with a power of 80 % and a significance level of 0.05. The unpublished pilot data on the effects of retro-walking on these variables was used to calculate SD’s. We assume a clinically important difference between two intervention groups of 1.08 in NRS score (*SD* = 1.19) and 4.47 points in functional score assessed using the reduced WOMAC index (*SD* = 4.9). The sample size calculation resulted in 20 participants in each group, or 60 total participants. To allow for a potential follow-up loss of 15 %, we will recruit a minimum of 69 participants.

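### The between-group test is a one-way ANOVA with no baseline covariate and an unstated dependent variable; ANCOVA on each outcome's own baseline would be more precise at almost no cost

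*Protocol article*

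**What the plan says.** All references are to the protocol article.

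- **Outcome measures** fixes two time points for every outcome: "All measurements will be taken at baseline (week 0), and at the end of the intervention (week 6".
- **Statistical analysis** uses baseline values first in a comparability display: "Demographic data and baseline scores of all outcome measures will be presented to evaluate baseline comparability of treatment groups".
- The same section then gives a descriptive summary: "Descriptive data will be reported for each group as the mean change in the outcome measures at baseline and at the end of the trial".
- For interval or ratio data it names the tests: "Paired t-tests and one-way ANOVA with Bonferroni adjustment for multiple comparisons will be applied to compare within and between group differences of all outcomes". It names no covariate, and it does not say whether the ANOVA's dependent variable is the week-6 score or the change from baseline.
- **Sample size** plans "with a power of 80 % and a significance level of 0.05". For pain it assumes a "clinically important difference between two intervention groups of 1.08 in NRS score", and the SD used there is 1.19. For function, the corresponding reduced WOMAC difference is 4.47 and its SD is 4.9. It arrives at 20 per group and recruits 69. The SDs come from unpublished pilot data, and the text does not say whether they are SDs of a score at one visit or of a change.

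**The concern.** A one-way ANOVA has one factor and no covariate. Each outcome has its own week-0 value, which is usually the best available predictor of the week-6 value. Leaving it out of the model keeps variance in the error term that could be removed. With about 20 to 23 patients per arm, it also means that a chance difference in baseline pain or function is not handled well:

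- an ANOVA of week-6 scores makes no adjustment for it;
- an ANOVA of change scores subtracts baseline with a fixed slope of 1, which over-corrects when the baseline to week-6 correlation is below 1.

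A table of baseline characteristics shows such a difference but does not adjust the treatment estimate for it. At stake are power, the width of the confidence intervals, and the accuracy of the estimate given the baseline balance that actually occurs.

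**Working it through.** **Inputs from the documents.** NRS difference 1.08, SD 1.19, so d = 1.08/1.19 = 0.908. Reduced WOMAC difference 4.47, SD 4.9, so d = 4.47/4.9 = 0.912. Power 80%, alpha 0.05, 20 per group, 69 recruited (23 per group if split equally).

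**Assumptions.** The baseline to week-6 correlation r is not given, so 0.3, 0.5 and 0.7 are used. Variances are taken as equal at the two visits. Bonferroni is applied to three pairwise contrasts, alpha 0.05/3 = 0.0167, two-sided.

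**Step 1: the plan's own figure.** A two-sample t-test at two-sided 0.05 with 20 per group has power 79.9% (NRS) and 80.3% (WOMAC). The stated 20 per group reproduces, so the design was sized for one unadjusted two-group comparison and does not rely on baseline adjustment.

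**Step 2: residual variances**, in units of the single-visit variance:

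- week-6 score: 1
- change score: 2(1 − r)
- ANCOVA: 1 − r²

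The ratio of ANCOVA to week-6 is 1 − r². The ratio of ANCOVA to change is (1 − r²)/[2(1 − r)] = (1 + r)/2.

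| r | ANCOVA / week-6 | reduction | ANCOVA / change | reduction |
|---|---|---|---|---|
| 0.3 | 0.91 | 9% | 0.65 | 35% |
| 0.5 | 0.75 | 25% | 0.75 | 25% |
| 0.7 | 0.51 | 49% | 0.85 | 15% |

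**Step 3: power for the NRS contrast at 0.0167.** Noncentral t, with noncentrality (1.08/SD\*) × √(n/2). The error df are 3n − 3 for ANOVA and 3n − 4 for ANCOVA. SD\* is 1.19 for the unadjusted ANOVA. For ANCOVA it is 1.19√(1 − r²) if the stated SD is that of the week-6 score, or 1.19√[(1 + r)/2] if it is that of the change.

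Example, n = 20 and r = 0.5: SD\* = 1.19 × √0.75 = 1.031; noncentrality = (1.08/1.031) × √10 = 3.31; df 56; power 79.8%.

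| n per group | ANOVA | ANCOVA, SD of week-6 score (r = 0.3 / 0.5 / 0.7) | ANCOVA, SD of change (r = 0.3 / 0.5 / 0.7) |
|---|---|---|---|
| 20 | 65.7% | 70.4% / 79.8% / 93.6% | 85.9% / 79.8% / 73.9% |
| 23 | 73.1% | 77.7% / 86.0% / 96.6% | 91.0% / 86.0% / 80.8% |

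The WOMAC figures are within about one percentage point. The calculation charges one df for the covariate and ignores the small further cost of estimating its slope.

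**Step 4: chance imbalance.** At 20 per arm the standard error of a baseline difference between two arms is √(2/20) = 0.316 SD. A difference above 0.5 SD has probability 11% for a given pair and about 25% for the largest of the three pairs (simulation). Given a baseline difference δ, the expected shift in the unadjusted comparison is rδ for week-6 scores and −(1 − r)δ for change scores. With δ = 0.5 SD and r = 0.5 these are +0.25 SD and −0.25 SD, against a planned effect of 0.91 SD.

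**The case against.** **A reader might infer that baseline is merely inspected and then discarded.** The text does not support that. Baseline enters the mean-change summaries and the paired t-tests, and it would be subtracted for every patient if the ANOVA is run on changes, which is a natural reading of the section. On that reading imbalance is not left unadjusted; it is over-adjusted. What stands is that no covariate is named and the dependent variable is left open.

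**A reader might also infer that the planned test is biased or the sample size wrong on this ground.** Neither follows. Randomisation keeps the unadjusted comparison unbiased on average, and the 20 per group reproduces without any adjustment. The shifts in Step 4 are conditional on an imbalance having occurred.

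**The gain rests on a correlation that the documents do not give.** This stands. At 20 per group it is only about 5 points on the week-6 reading with r = 0.3, and about 8 points on the change reading with r = 0.7. Restoring roughly 80% power is the result at r = 0.5, not a general one.

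**Twenty per group is the figure after full attrition.** This also stands. Statistical analysis specifies intention-to-treat with last observation carried forward, so all 69 may be analysed; the 23-per-group row covers that case, setting aside any effect of carrying values forward on the difference or the SD.

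**Lack of stratification is weak support.** The randomisation section describes none, but an article may leave list generation to the full protocol. The point does not depend on it. Nor should the loss of power from Bonferroni be counted as part of this point; it is a separate sample-size matter and serves here only as the common reference level.

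**Conclusion.** The point holds as one of efficiency and of accuracy given the observed baseline balance. The protocol names a between-group model without a baseline covariate and does not fix its dependent variable, although the covariate is collected for every outcome. ANCOVA has the smaller residual variance under either reading, for every r examined. For the NRS contrast at 0.05/3, the gain is about 5 to 28 percentage points of power with 20 per group (65.7% to between 70.4% and 93.6%), and about 5 to 24 points with 23 per group (73.1% to between 77.7% and 96.6%).

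The direction is secure apart from the negligible loss of one degree of freedom. The size is not: it depends on the assumed r of 0.3 to 0.7, on equal variances at the two visits, and on which SD the pilot data supplied.

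**What to change.** In Statistical analysis, make the primary between-group analysis of each interval-scale outcome an ANCOVA of the week-6 value, with group as factor and that outcome's baseline value as covariate. Report adjusted mean differences with confidence intervals for the three Bonferroni-adjusted pairwise contrasts, and keep the unadjusted one-way ANOVA as a supportive analysis, stating whether it uses week-6 or change scores.

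The cost is a sentence or two of text and one degree of freedom per outcome. It needs no extra patients, visits or measurements, and the planned SPSS software can fit the model. It also settles which form of the outcome the main comparison uses.

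### The protocol does not fix which test family analyses the two primary scores, and its rank-based route names a related-samples test for three independent arms

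*Protocol article*

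**What the plan says.** The Statistical analysis section announces "Data normality will be tested". It names no test, does not say whether raw scores, changes or residuals are tested, and attaches no consequence to the result.

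Two families follow. Paired t-tests and one-way ANOVA with Bonferroni adjustment are given for all outcomes, with interval/ratio data in brackets. The second family reads: "The Wilcoxon signed-rank test and Friedman test will be used to compare within and between group differences of all outcome measures (nominal/ordinal data". Each sentence claims every outcome, and the bracketed data type is the only thing that separates them.

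The outcome sections do not settle the type. The NRS is described as a 0 to 10 scale, and the reduced WOMAC as items on a five-point Likert response scale. Neither is called interval or ordinal.

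The Sample size section is in means and SDs: "We assume a clinically important difference between two intervention groups of 1.08 in NRS score", with SD 1.19, and "4.47 points in functional score assessed using the reduced WOMAC index", with SD 4.9.

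**The concern.** A single-item 0 to 10 rating and a sum of Likert items can each be defended as interval or as ordinal. The written selector therefore does not decide the test for either primary outcome, and the choice could be made after the data are seen. The normality test is the only other criterion in the paragraph, so an analyst might well use it as the tie-breaker.

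Three things are at stake:

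- The primary test would depend on the data or on the analyst.
- The rank tests named do not estimate a difference in points, so they do not test the quantity on which the trial was sized.
- On the rank route, the between-group test named is Friedman, which compares related samples. Here the arms are three separately randomized groups, so no related-samples structure exists.

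**Working it through.** **1. Which analysis was powered?** Inputs from the Sample size section: "with a power of 80" per cent, "and a significance level of 0.05" (two-sided assumed, as sidedness is not stated), and the differences and SDs above.

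n per group = 2 × (1.960 + 0.842)² × (SD / difference)²

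- NRS: 2 × 7.849 × (1.19 / 1.08)² = 15.70 × 1.214 = 19.1, rounded up to 20.
- WOMAC function: 15.70 × (4.9 / 4.47)² = 15.70 × 1.202 = 18.9, rounded up to 19.
- The exact two-sample t-test gives 20.07 and 19.87, with power 79.9% and 80.3% at 20 per group.

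The protocol's 20 per group is reproduced as a comparison of two means. Only the parametric route matches it.

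**2. What if the normality result chose the route for NRS?** This was simulated. The assumptions, not stated in the protocol, are scores drawn from a normal distribution, rounded to whole numbers and limited to 0-10, with tests at 0.05. The SD of 1.19 and the arm sizes (20 analysed, 69/3 = 23 recruited) are the protocol's.

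| Shapiro-Wilk rejects | 20 per arm | 23 per arm |
|---|---|---|
| At least one of three arms, SD 1.19 | 87-90% | 92-94% |
| Pooled residuals, SD 1.19 | 42-46% | 50-55% |
| At least one arm, SD 1.5 (assumed), arm means 3 or higher | 64-65% | 68-72% |
| At least one arm, SD 2.0 (assumed), arm means 3 or higher | 37-40% | 41-49% |

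The 55% comes from a setting with one arm mean at 2; in the others the upper end is about 51%. At SD 2.0 with one arm mean at 2, the any-arm figure rises to 72% (20 per arm) and 82% (23 per arm). A Lilliefors test in place of Shapiro-Wilk gives about 98% (any arm) and 74-77% (residuals) at SD 1.19 and 20 per arm.

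As a control, unrounded normal scores are rejected in at least one arm in about 13% of trials, close to the 1 − 0.95³ = 14% expected from three tests at 5%. The excess at SD 1.19 comes from rounding, not from any failure of a comparison of means.

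**3. The same question for WOMAC function.** Assumed: whole-number score 0-28 (seven items coded 0-4), SD 4.9, one arm better by 4.47, 20-23 per arm. Away from the floor, Shapiro-Wilk rejects in at least one arm in about 15-19% of trials and on residuals in 4-7%. With one arm mean at 5.5 the figures are 34-41% and 10-11%.

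**4. What does each route cost for NRS?** Power with one arm better by 1.08, SD 1.19, whole-number scores, 20-23 per arm:

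- One-way ANOVA: about 80-87%.
- Kruskal-Wallis: about 78-85%.
- Friedman, with participants matched across arms arbitrarily so that it can be run: about 72-78%.

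A valid rank test thus loses about 1-3 points, and Friedman about 8-9.

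**5. Type I error with no true difference.** ANOVA alone gives 5.0-5.2%. Letting the Shapiro-Wilk result choose the route gives 4.9-5.0%. Claiming success if either route is significant gives 5.8-6.0%.

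**The case against.** The strongest objection is that the protocol contains no normality gate. It says that normality will be tested and stops; the written criterion is data type. The choice of normality test and what follows from it are matters that an SAP, not shown here, could settle. This stands. A reader might infer that the normality test would usually move the primary pain outcome off its mean-difference analysis, but the documents do not support that. The switch is not written, and whole-number NRS recording is an assumption. The word *usually* also depends on testing each arm separately at SD 1.19: on pooled residuals, the natural unit for ANOVA, rejection occurs in about half of trials or fewer with Shapiro-Wilk.

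A reader might also extend the argument to WOMAC function. The figures in step 3 do not support that except near the floor.

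The numerical harm from a valid rank test is small, and type I error barely moves. The larger power loss belongs to Friedman, not to normality testing. The protocol also promises group mean changes whichever test is used, so a difference in points could be obtained by subtraction, though with no confidence interval promised.

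Finally, baseline adjustment does not follow from the normality question; it is a separate improvement.

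Two defects survive all of this because they are in the stated text. Two families are each assigned every outcome with a selector that does not classify the primary scores, and a related-samples test is named for a between-group comparison. An SAP could repair both, but the protocol as written would still be wrong on the second.

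**Conclusion.** The point holds in a limited form. The primary analysis of NRS and reduced WOMAC is not fixed, one of the two routes on offer has no valid between-group test, and only the other matches the sample size calculation. The Friedman error and the unclassified scores rest on the text alone.

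The size of any normality-driven switch is conditional on three things: that the result is used as a switch, that NRS is recorded in whole numbers, and that the SD is near 1.19. Under all three, about 87-93% of trials would fail a per-arm Shapiro-Wilk test, against about 42-51% on pooled residuals; at SD 2.0 the per-arm figure is about 35-48% away from the floor. The main consequence is an open choice of primary test and a change in the quantity tested, not a large loss of power. It should be corrected before any outcome data are seen.

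**What to change.** State that NRS and reduced WOMAC scores are compared between arms with one linear model, containing arm and baseline score, whatever any normality test shows. Report mean differences with 95% confidence intervals, and apply the Bonferroni adjustment already planned to the pairwise comparisons. The results can then be read directly against 1.08 and 4.47. If normality is examined at all, look at model residuals graphically and attach no change of primary test to what is seen.

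Replace Friedman with a rank test for independent groups: Kruskal-Wallis overall, Mann-Whitney for pairs. Label it a sensitivity analysis.

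The cost is a rewording of the Statistical analysis section. Baseline scores are already collected, and no further participants or measurements are needed.

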### Hypotheses

The retro-walking training will reduce pain and improve quadriceps muscle strength, function, and mobility in subjects with knee OA.The forward-walking training will reduce pain and improve quadriceps muscle strength, function, and mobility in subjects with knee OA.The effects of the retro-walking will be greater compared to forward-walking in improvements of quadriceps muscle strength, pain, function, and mobility in subjects with knee OA.

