## Methods/Design

### Trial design

This trial is a three-arm assessor-blinded randomized controlled trial (RCT) comparing retro-walking to forward-walking or control. All experiments will follow the Declaration of Helsinki. The protocol follows the CONSORT guidelines for reporting of non-pharmacological interventions [30].

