## Interventions

### Standard physiotherapy program

All the participants will receive a supervised standard physiotherapy training program at the outpatient physiotherapy department as reported in a previous study [33]. The exercise program will comprise a combination of OKC and CKC exercises, including isometric quadriceps, terminal knee extension, isometric hip adduction exercise, straight leg raising exercise, leg press, and semi-squat. In a recent systematic review, Anwer et al. [34] reported the use of a combination of OKC and CKC exercises in the management of subjects with knee OA. All the participants will also receive Ultrasound therapy (1.5 W/cm2 for 7 min in continuous mode) around the knee joint before exercise. A previous study suggested that the continuous mode of therapeutic ultrasound is an effective and safe treatment modality in reducing pain and improving function in subjects with knee OA [35]. The participants will perform prescribed exercises for 6 weeks (3 days/week) as previously reported [33]. All the participants will be restricted to perform a home exercise or walking program other than the prescribed program.

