### Control group

The participants in group C will receive only a supervised standard physiotherapy program as mentioned above.

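### Hypotheses 1 and 2 name no comparator and the deciding test is not fixed, so a walking effect could be declared from within-arm paired tests when walking adds nothing to physiotherapy

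*Protocol article*

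**What the plan says.** Under Hypotheses, the first reads "The retro-walking training will reduce pain and improve quadriceps muscle strength, function, and mobility in subjects with knee OA" and the second "The forward-walking training will reduce pain and improve quadriceps muscle strength, function, and mobility in subjects with knee OA". Neither names a comparator. Only the third does, and its comparator is the other walking arm: "The effects of the retro-walking will be greater compared to forward-walking in improvements of quadriceps muscle strength". No hypothesis mentions the control group.

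The interventions section gives active treatment to all three arms: "All the participants will receive a supervised standard physiotherapy training program at the outpatient physiotherapy department" and "All the participants will also receive Ultrasound therapy". The control arm differs only in having no walking: "The participants in group C will receive only a supervised standard physiotherapy program as mentioned above".

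Under Statistical analysis, for interval or ratio data, "Paired t-tests and one-way ANOVA with Bonferroni adjustment for multiple comparisons will be applied to compare within and between group differences". For nominal or ordinal data the named tests are the Wilcoxon signed-rank and Friedman tests. A level of 0.05 applies to all tests as the mark of significance. Descriptive mean change per group is promised separately, so the paired tests are meant as inference. The section does not say which test settles which hypothesis.

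**The concern.** A before-after change in a walking arm combines any effect of walking with the effects of the exercise programme and ultrasound, the natural course of symptoms, and regression to the mean. A paired test asks only whether the total differs from zero. The protocol itself cites evidence that ultrasound reduces pain and improves function, so it expects some improvement without walking.

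As worded, hypotheses 1 and 2 match the paired test at least as well as the between-arm test. A report could therefore cite a significant paired result in each walking arm as confirming both hypotheses, without using the control arm. A second risk is that a significant change in one arm and a non-significant change in another would be read as a difference between arms, which it is not.

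At stake is the main conclusion. The Discussion says that the trial will help to show whether one or both walking programmes are efficacious, and only the comparison with control can show that.

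**Working it through.** **Inputs from the protocol.** Sample size section: NRS difference 1.08 with SD 1.19, reduced WOMAC difference 4.47 with SD 4.9, power 80%, level 0.05, 20 per group, 69 recruited. Statistical analysis section: level 0.05 for all tests.

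**Assumptions.** Tests are two-sided. The 69 participants split equally, 69/3 = 23 per arm, all analysed (the plan carries the last observation forward). The improvement shared by all arms is not given, so 0.25 to 1.5 NRS points are shown. The SD of change is not given either: the protocol does not say whether 1.19 is the SD of a change or of a single score. Both 1.19 and a larger value of 2.0 are shown.

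**Step 1: the plan's own figure.** For two means, n per arm = 2 × [(1.960 + 0.842) × SD / difference]².
- NRS: 2 × (2.802 × 1.19/1.08)² = 19.1, rounded up to 20.
- WOMAC: 2 × (2.802 × 4.9/4.47)² = 18.9, rounded up to 19.

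The exact t-test power at 20 per arm is 79.9% (NRS) and 80.3% (WOMAC). The stated 20 per group reproduces, and this point does not rest on a sample-size error.

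**Step 2: the paired test when walking adds nothing.** If every arm improves by c points, the paired t statistic in a walking arm has noncentrality c × √23 / SD on 22 degrees of freedom and critical value 2.074. For c = 1.0 and SD = 1.19 this is 1.0 × 4.796/1.19 = 4.03, and the test is significant with probability 97%.

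| Shared NRS improvement (assumed) | Change SD 1.19 | Change SD 2.0 |
|---|---|---|
| 0 | 5% | 5% |
| 0.25 | 16% | 9% |
| 0.5 | 49% | 21% |
| 1.0 | 97% | 63% |
| 1.5 | >99% | 93% |

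With 20 per arm and SD 1.19, the probabilities at 0.25, 0.5 and 1.0 points are 15%, 43% and 95%.

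**Step 3: the same situation judged between arms.** In 20,000 simulated trials of three identical arms (20 per arm, change SD 1.19), the unadjusted retro-versus-control t-test was significant in about 5% at shared improvements of 0.5, 1.08 and 1.5 points alike. At 0.05/3, the chance that either walking arm differed significantly from control was about 3%. At a shared 1.08 points, by contrast, the paired tests were significant in both walking arms in 94% of trials, and in all three arms in 92%. The shared improvement cancels between arms and does not cancel within them.

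**Step 4: what the between-arm route can detect.** If the sample-size differences are taken to apply to walking versus control, the exact t-test power at 0.05/3 and 20 per arm is 64% (NRS) and 65% (WOMAC). At 23 per arm it is 72%. By the formula in Step 1, with 1.960 replaced by 2.394, 80% power needs 2 × (3.236 × 1.19/1.08)² = 25.4, rounded up to 26 per arm.

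**The case against.** The strongest reply is that the comparison with control is already planned. The same sentence that names the paired tests names a one-way ANOVA with Bonferroni adjustment, whose pairwise comparisons include each walking arm against control. The trial design section describes the study as "comparing retro-walking to forward-walking or control", and the sample size rests on a difference between groups, not on change from baseline. Paired tests beside a between-group test are not wrong in themselves, and the rule for deciding each hypothesis might be in a fuller plan that is not shown.

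Most of this stands, and it limits the claim. A reader might infer that the hypotheses are explicitly about within-arm change, or that a walking effect would be declared from the paired tests. The documents do not support either. The hypotheses leave the comparator open without specifying change from baseline, and nothing says that the paired tests decide them. Nor should the 63% to 99% results be read as the trial's false-positive rate. They hold only if the paired test decides and the shared improvement is 1.0 to 1.5 points. At 0.25 to 0.5 points the range is about 9% to 49%. A count of unadjusted paired tests would also go too far, because the sentence does not clearly confine the Bonferroni adjustment to the ANOVA.

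The reply does not remove the point. The hypotheses and the named tests are the article's own content, and a planned ANOVA does not stop significant paired results from being reported as confirming hypotheses 1 and 2 as worded. The between-arm route is also weaker than it looks. If the NRS or the Likert-scored WOMAC is treated as ordinal, the named between-group test is Friedman's, which is for related samples and does not fit three independent arms. The signed-rank test would then be the only usable test as written.

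**Conclusion.** The point holds as a gap in how the hypotheses are tied to the tests. Hypotheses 1 and 2 have no comparator, every arm receives active treatment, and within-arm tests are planned as inference at 0.05 beside a between-group test, with nothing to say which decides. A walking effect could therefore be declared when walking adds nothing.

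If the paired test were used to decide, the false-positive chance in one walking arm would run from about 9% to over 99% across the assumed shared improvements of 0.25 to 1.5 NRS points and change SDs of 1.19 and 2.0. A walking-versus-control contrast holds it at about 5% or below. The direction does not depend on the assumptions: any shared improvement above zero lifts the paired test's error above 5% and leaves the between-arm contrast unaffected. The size depends on both the shared change and the SD of change, and the protocol fixes neither.

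**What to change.** Restate hypothesis 1 as retro-walking versus control and hypothesis 2 as forward-walking versus control. Add one sentence to the statistical analysis section: these hypotheses are decided only by the between-arm contrasts of change that the planned analysis already makes available. Drop the paired t-tests and signed-rank tests as inference, and report mean change within each arm with a 95% confidence interval, labelled as descriptive. If ordinal methods are kept as an alternative, name a between-group test for independent arms so that the decisive contrast exists on that route too.

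This needs edits to two hypotheses and to the analysis paragraph, and no further data. The limit to state openly is power: about 64% at 20 evaluable per arm for a Bonferroni contrast at 0.05/3, if the sample-size differences are taken to apply to walking versus control. The planned ANOVA comparisons already have this limit. The change makes it visible, because hypotheses 1 and 2 would then rest on those contrasts alone.

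### With outcomes measured only at baseline and week 6, last observation carried forward scores every missing participant as zero change, which dilutes the group difference or biases it in either direction

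*Protocol article*

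**What the plan says.** Three statements in the protocol article meet here.

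- Outcome measures: "All measurements will be taken at baseline (week 0), and at the end of the intervention (week 6"). No other outcome assessment is described.
- Statistical analysis: "The intention-to-treat principles will be used for analysis", and then "For missing data, the last observation carried forward method will be used". No alternative method and no sensitivity analysis is named.
- Sample size: "To allow for a potential follow-up loss of 15 %, we will recruit a minimum of 69 participants". Missing week 6 data are therefore expected.

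The planned comparisons are paired t-tests within groups and one-way ANOVA with Bonferroni adjustment between the three groups. For pain, the planning value is stated as a "clinically important difference between two intervention groups of 1.08 in NRS score"; the SD attached to it is 1.19. For function on the reduced WOMAC, the planning difference is 4.47, with an SD of 4.9.

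Under Interventions, every group, including control, receives the supervised exercise programme with ultrasound. The Hypotheses section expects improvement in both walking groups.

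**The concern.** Carrying a value forward needs an earlier post-baseline value to carry. Here there is none, so the rule becomes baseline carried forward, and each lost participant enters the analysis with a change of zero as if it had been observed. That does not fit a trial in which every arm is treated and at least two arms are expected to improve.

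Two consequences follow. If loss is the same in every arm, the estimated difference shrinks by the fraction lost. If loss differs between arms, the rule produces a between-group difference that reflects attendance rather than treatment. Unequal loss is possible: the walking arms carry extra training time that control does not, and the article itself lists training-related knee pain as an adverse effect. The rule applies to both primary outcomes, both secondary outcomes, and the within-group as well as the between-group tests.

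**Working it through.** **Inputs from the article.** NRS difference 1.08, SD 1.19; reduced WOMAC function difference 4.47, SD 4.9; "a significance level of 0.05"; power 80%; 20 per group; 15% loss; 69 recruited, that is 69/3 = 23 per arm if allocation is equal.

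**Assumptions, because the article gives no figure.** The stated SD applies to change scores; dropout is unrelated to outcome; per-arm dropout and mean improvement are varied over a range.

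**Step 1: the plan's own figure.** A two-sided two-group comparison at 0.05 with 80% power needs 20 per arm for NRS and 19 for WOMAC by the normal formula. Exact noncentral-t power at 20 per arm is 79.9% and 80.3%. The stated 20 per group reproduces.

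**Step 2: what the rule estimates.** With mean changes μA and μB and dropout dA and dB, the expected difference is (1 − dA)μA − (1 − dB)μB.

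Equal 15% loss:
- NRS: 0.85 × 1.08 = 0.918
- WOMAC function: 0.85 × 4.47 = 3.80

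Within-group mean changes shrink by the same factor.

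**Step 3: variance.** An arm's change score is a mixture with variance (1 − d)σ² + d(1 − d)μ². This exceeds σ² only if μ > σ/√(1 − d) = 1.19/√0.85 = 1.29 points. Below that, the imputed zeros reduce the variance, and any power loss comes from the dilution.

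**Step 4: power with equal 15% loss.** True NRS difference 1.08, 23 per arm, unadjusted two-group t-test at 0.05, by simulation:

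| Reference-arm improvement (assumed) | Power with baseline carried forward |
|---|---|
| 0 | about 77% |
| 0.5 | about 74% |
| 1 | about 69% |
| 1.5 | about 63% |
| 2 | about 56% |

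Analysing completers only (0.85 × 23 = 19.55 per arm) gives 79%. The Bonferroni step is left out of all these figures, so they compare the two ways of handling missing data and are not the trial's actual power. With equal loss and no true effect, type I error stays at about 5%.

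**Step 5: unequal loss with no true difference.** With a common improvement of 2 NRS points, the false difference is 2 × (dB − dA):
- 10% versus 20%: 2 × 0.10 = 0.20
- 5% versus 25%: 2 × 0.20 = 0.40

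Rejection rates by simulation, 23 per arm, with 15% loss assumed in the third arm:

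| Loss in the two arms compared | Bonferroni pairwise test (nominal 1.7%) | Omnibus ANOVA (nominal 5%) |
|---|---|---|
| 10% vs 20% | about 3% | about 7% |
| 5% vs 25% | about 9% | about 14% |

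**Step 6: direction when the 1.08 difference is real.** With a comparator improvement of 2 points:
- 20% lost in retro-walking, 10% in forward-walking: 0.80 × 3.08 − 0.90 × 2 = 0.66
- 10% and 20%: 0.90 × 3.08 − 0.80 × 2 = 1.17
- 25% and 5%: 0.75 × 3.08 − 0.95 × 2 = 0.41
- 5% and 25%: 0.95 × 3.08 − 0.75 × 2 = 1.43

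The same rule can therefore understate or overstate the effect.

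**The case against.** The strongest reply is that the size of the problem depends on quantities the article does not give. All three arms share the same supervised programme, so a large dropout imbalance is possible but not shown. With no improvement in the reference arm, power is about 77% against 79%, which hardly matters. With equal loss and no true effect, the error rate is right. All of this stands, and it is why the results are given as ranges.

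Four stronger readings are tempting but not supported.

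- *Type I error of 18% instead of 5%.* That figure arises at 5% versus 25% loss from a single unadjusted two-group t-test. The article plans ANOVA with Bonferroni adjustment, for which Step 5 gives the relevant rates. Inflation remains, but at a different size and against a different nominal level.
- *Zero change is implausible for those who drop out.* The expected improvement concerns people who are treated. Those lost may be the ones who did not improve or had more pain. The objection is to fixing the value at exactly zero for everyone without examining it. The assumption that dropout is unrelated to outcome is not supported by the article either.
- *Imputed zeros always inflate the variance.* This holds only above about 1.3 points of mean improvement (Step 3).
- *The 15% allowance contradicts the missing-data rule.* It does not. Recruiting extra participants to offset lost information is ordinary under any missing-data method, and the article does not say that lost participants leave the analysis.

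**Conclusion.** The concern holds. The two measurement times and the carry-forward rule are both fixed in the text, so zero change for every participant missing at week 6 is a stated consequence and not a detail left to another document.

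The 15% dilution under equal 15% loss (1.08 to 0.92 on the NRS) is exact given dropout unrelated to outcome. The power loss ranges from slight to more than 20 percentage points (79% to 56%), depending on an assumed reference-arm improvement of 0 to 2 points. Under unequal loss, the false difference and the excess rejections depend on assumed per-arm rates: modest at 10% versus 20%, material at 5% versus 25%. Because the direction depends on which arm loses more participants, the rule cannot be defended as conservative.

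**What to change.** In Statistical analysis, replace last observation carried forward as the primary method with one of:
- a likelihood-based model of the baseline and week 6 values that includes all randomised participants, with a common baseline mean across arms; or
- multiple imputation by arm, using baseline and the other outcomes.

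Keep zero-change imputation only as a sensitivity analysis, beside a delta-adjusted analysis in which the imputed week 6 values are shifted over a stated range, because dropout may be related to outcome. Report the number lost and the reasons by arm.

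The cost is a change of wording and a little more analysis work. SPSS can fit both options, and no visit is added. The primary analysis would then rely on a missing-at-random assumption, which the sensitivity analyses are there to test. Seeking a week 6 assessment from participants who stop training would also help, but that changes trial conduct and should be decided separately.
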